### Sample size

The sample size is 60 subjects (20 subjects in each group). As we did not retrieve an appropriate study, according to Cohen’s theory [17], the effect size of 0.25 was applied. G*Power was used to estimate the sample size (repeated measures analysis of variance (ANOVA), within-between interaction) with effect size = 0.25, *α* = 0.05, 1 − β = 0.95, and the number of groups = 3. The total sample size based on the result was 54 (18 subjects per group). Considering 10% attrition, we inflated the total sample size to 60.

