## Statistical methods

Normally distributed variables will be presented by means with standard deviations, and nonnormally distributed data will be presented by medians with interquartile ranges. Categorical variables will be presented by proportion and frequency.

Investigators in charge of the result analysis will be blinded to the group allocation. All data will be analysed by Statistical Package for the Social Science (SPSS) version 26.0 software. The score of the primary outcome and secondary outcomes will be measured at different time points for the same subject. Two-factor repeated-measures analysis of variance (ANOVA) will be used for the statistical analysis for all outcomes with the sphericity test before analysis. If the data is dissatisfied with the sphericity test, the Green-house-Geisser method will be used to correct it. Simple effects tests will be used for the further exploration of interaction effects by time and group. Scheirer-Ray-Hare test will be used if the data are not satisfied with normal distribution. The statistical difference will be set at a *P* value less than 0.05.

The subgroup analysis will be conducted for further exploration. The comparison will be conducted between people with the first stroke onset for less than three months and residual people in terms of the score of FMA-UE. We will test whether RTFE shows the same effectiveness in people with different durations after first stroke onset by two-factor repeated measures ANOVA with the same statistical difference.

All analyses in this trial will follow the intention-to-treat principle. Based on this principle, all participants no matter what kind of intervention they received will be regarded as randomized. Multiple imputations based on 5 replications and the Markov-chain Monte Carlo method in the SAS MI procedure will be used to handle the missing data.

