## Discussion

We suppose that this trial will reveal the effectiveness of RTFE on upper limb dysfunction after stroke. One experiment conducted by Meadmore investigated the FES mediated by iterative learning control plus robotics in reducing motor impairment in 5 chronic stroke patients [15]. A significant improvement was observed after 18 RT sessions in subjects. Our RCT will provide evidence of comparison among three groups and further explore the reliability of this conclusion with a bigger sample size. Although FES in our study is based on the open-loop design, considering this is the most widely used FES and most FES with new-type controllers are still immature, this might be the easiest protocol to implement, which makes the result of our trial with high practical value. Straudi’s recent study investigated robot-assisted hand training with FES in improving the hand function of stroke patients [11]. The result shows an equivalent improvement between the RTFE group and the CRT group. Our trial focuses on the proximal joints of the upper limb, and the result of this trial will reveal the influence of RTFE on shoulder, elbow, and wrist neuromuscular function after stroke.

There are several strengths and weaknesses of this trial. Firstly, compared with previous self-controlled study, this study is a well-structured 3-arm RCT. Our study compares the effect between RTFE with RT alone to explore the overlapping effect of this combination therapy. Then, this study adopts various methods to reduce the bias and enhance the reliability as possible. Considering the difference of neuroplasticity potential in stroke survivors at different stages, stratification by baseline of time after the first-ever stroke is used to reduce the heterogeneity among the three groups. The use of a randomized block design reduces the bias and promotes balance in the allocation. The systematic imputation strategies further guarantee data and conclusion’s reliability. Additionally, the use of intention-to-treat analysis reduces the selection bias. Although not all interveners and participants are blinded, the blinding still covers assessors, RT therapists, CRT therapists and participants in the RT and RTFE groups for reducing potential bias.

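### The early-versus-late subgroup question asks about sameness, but its only tool is a difference test at p < 0.05, which cannot support a conclusion of sameness at this sample size

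*Protocol article*

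**What the plan says.** The subgroup paragraph of Statistical methods opens with "The subgroup analysis will be conducted for further exploration". It then defines the split on FMA-UE: "The comparison will be conducted between people with the first stroke onset for less than three months and residual people". The question follows: "We will test whether RTFE shows the same effectiveness in people with different durations after first stroke onset by two-factor repeated measures ANOVA". The criterion is carried over from the main analysis ("by two-factor repeated measures ANOVA with the same statistical difference"), where the plan sets it: "The statistical difference will be set at a *P* value less than 0.05".

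The Sample size section fixes the numbers: "The sample size is 60 subjects (20 subjects in each group", with 54 needed before 10% attrition. That calculation is for the overall group-by-time interaction. Randomization is stratified at the same 3-month cut, but the stratum sizes are not fixed.

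**The concern.** The question and the tool do not match. The question is whether the effect is the same in two strata. The tool tests the null hypothesis that it is the same. Rejection answers that it is not. Failure to reject answers nothing unless the interval around the difference is narrow, and the paragraph names no interval and no other criterion.

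With about ten patients per arm and stratum, failure to reject is the likely result even when the effects differ moderately. A reader of the trial report could then conclude that adding FES to robot training works as well late as early, on data that could not exclude a large difference. The mismatch remains whichever model terms are fitted, including the correct arm-by-stratum contrast.

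**Working it through.** **Inputs from the protocol.** 3 arms, 20 per arm planned and 18 per arm after attrition; 3 assessments; α = 0.05; planning effect size f = 0.25 with power 0.95; strata < 3 and ≥ 3 months; FMA-UE minimal clinically important difference 12.4; entry scores 11 to 33.

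**Assumptions (not in the protocol).** Strata split 50:50, with 30:70 as the uneven case. 1 SD is the SD of the analysed score; at a correlation of 0.5 with baseline, the change score has the same SD as the raw score. Tests are two-sided.

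**1. The plan's own figure.** For the within-between interaction, λ = f²·N·m/(1 − ρ), with df (k − 1)(m − 1) and (N − k)(m − 1). With k = 3, m = 3, ρ = 0.5 and no sphericity correction, N = 54 gives λ = 0.0625 × 54 × 3 / 0.5 = 20.25 on 4 and 102 df. Power is 0.958. Then 54/0.9 = 60. The stated 54 and 60 reproduce, but for the overall interaction, not for the subgroup question.

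**2. Precision of the subgroup contrast.** The quantity of interest is the RTFE-minus-RT effect in one stratum minus that in the other. With a and b patients per arm in the two strata:

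SE = SD × √(2/a + 2/b); half-width = t(0.975) × SE, with df from the four cells.

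| Analysed, split per arm | SE (SD) | df | Half-width (SD) | Missed, 0.5 SD | Missed, 1.0 SD |
|---|---|---|---|---|---|
| 60, 10/10 | 0.632 | 36 | 1.28 | 88.0% | 66.3% |
| 54, 9/9 | 0.667 | 32 | 1.36 | 88.7% | 69.3% |
| 60, 6/14 | 0.690 | 36 | 1.40 | 89.1% | 70.8% |
| 54, 5.4/12.6 | 0.727 | 32 | 1.48 | 89.8% | 73.4% |

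Miss rates are 1 minus non-central t power. Pooling the residual over all six cells instead gives half-widths of 1.27 to 1.46 SD and changes no conclusion. The three-way interaction in a repeated-measures ANOVA (ρ = 0.5) has 10 to 11% power for 0.5 SD.

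**3. Sensitivity to correlation.** If 0.5 SD refers to the raw score, the change-score SD is √(2(1 − ρ)) of it: 0.775 at ρ = 0.7 and 0.632 at ρ = 0.8. With 10 per cell the miss rate falls to about 83% and 77%.

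**4. Sensitivity to the size of the difference.** Take a 12.4-point early-late difference, 10 per cell and an assumed SD of 8 to 11. The standardized difference is 12.4/8 = 1.55 down to 12.4/11 = 1.13, and the miss rate is about 34 to 59%. On the same scale the half-width is 1.28 × 8 = 10.2 to 1.28 × 11 = 14.1 points. It exceeds 12.4 once the SD is above 12.4/1.28 = 9.7. From there upward, an observed difference of zero would not exclude 12.4 points.

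**5. The other reading of the test.** Early versus late within the RTFE arm alone (18 to 20 patients) misses 0.5 SD in about 81 to 85% of trials. At 12.4 points, SD 8 to 11 and 10 versus 10, it misses 9 to 34%. That comparison cannot separate an RTFE effect from different natural recovery early and late.

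**The case against.** The strongest reply is that the alleged misreading is not in the text. Nothing says that p ≥ 0.05 will be reported as equal effectiveness. Asking whether effects are the same is ordinary phrasing for a null of homogeneity, and the trial's primary null is framed in the same way. The paragraph calls itself exploratory, and no objective or conclusion claims equal effect across strata. All of this stands. A reader might infer that the protocol plans to declare equality on a non-significant result; the document does not support that.

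A reader might also take the Discussion's remark ("Considering the difference of neuroplasticity potential in stroke survivors at different stages") as a forecast that the RTFE effect differs by stage. It is given there as the reason for stratifying the randomization, so it does not bear that weight.

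Low power for a subgroup interaction is normal in a trial of 60, and the protocol sets no power target for this analysis. Low power alone is therefore no fault. The miss rates also depend on an effect size, stratum sizes and a correlation that the document does not give. That is fair, and the ranges above show it.

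The two factors of the ANOVA are not named. If they are group and time within each stratum, no early-late p-value exists at all. That weakens any claim about how the result would be read, but it leaves the sameness question with even less of an answer.

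Finally, intervals and margins may be left to an analysis plan that is not shown. The point does not rest on their absence. The protocol itself fixes both the question and the tool, and the two do not fit.

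**Conclusion.** The concern holds as a mismatch between question and method, of minor to moderate weight. At this size the stated test cannot support a conclusion of sameness: with roughly even strata, the interval for the between-stratum difference in effect would extend about 1.3 to 1.4 SD either side of the estimate, and up to about 1.5 SD with uneven strata. Moderate differences would usually go undetected, and even a 1.0-SD difference would be missed in about two thirds of trials or more. The half-width scales with the SD of the analysed score, so high correlation with baseline narrows it in FMA-UE points. The issue is confined to an exploratory subgroup analysis and leaves the primary comparison untouched.

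**What to change.** Replace the sentence that poses the question with, for example: *We will estimate the difference between strata (< 3 versus ≥ 3 months) in the RTFE-minus-RT effect on week-6 FMA-UE, with its 95% confidence interval; p ≥ 0.05 will not be interpreted as equal effectiveness.* The existing exploratory label can stay. A margin in FMA-UE points, fixed in advance, would be needed only if the authors wish to claim similarity; it is optional.

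The cost is one sentence and one reported interval, from data already being collected and with no extra patients. The trial gives up a sameness claim that it could not have supported.

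### The subgroup question about time since stroke is assigned a two-factor repeated-measures ANOVA with no arm-by-stratum term, so as written it does not test whether the effect of RTFE differs between early and late patients

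*Protocol article*

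**What the plan says.** All of this is in the protocol article.

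- **Main analysis (Statistical methods).** All outcomes are analysed by two-factor repeated-measures ANOVA. The two factors can be read from the follow-up step: "Simple effects tests will be used for the further exploration of interaction effects by time and group". The significance rule is: "The statistical difference will be set at a *P* value less than 0.05".
- **Subgroup analysis (Statistical methods).** It is introduced with: "The subgroup analysis will be conducted for further exploration". The contrast, on the Fugl-Meyer upper-extremity score (FMA-UE), is: "The comparison will be conducted between people with the first stroke onset for less than three months and residual people". The question and method are: "We will test whether RTFE shows the same effectiveness in people with different durations after first stroke onset by two-factor repeated measures ANOVA", at the same significance level. The two factors of this ANOVA are not listed, and no term combining arm with stratum is mentioned.
- **Stratification.** Randomization and blinding stratifies at the same 3-month cut. The Discussion gives the reason: "Considering the difference of neuroplasticity potential in stroke survivors at different stages". The inclusion criteria admit patients from 1 week to 1 year after stroke.
- **Comparator.** The secondary objective and the Discussion set RTFE against robot training alone (RT).

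**The concern.** In a randomised trial, effectiveness is a contrast between arms. Equal effectiveness in two strata means that the RTFE–RT contrast is the same in both. With repeated measures, that is the time × group × stratum interaction. At the primary time point it is arm by stratum on week-6 FMA-UE.

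A two-factor repeated-measures ANOVA in the section's own usage has time plus one between-patient factor. That leaves room for arm or for stratum, but not for both.

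At stake is the only prespecified effect-modification analysis, on the stratification factor and the primary scale. If it answers a different question, the report could attribute to RTFE a difference that belongs to the stage of recovery. It could also present one significant and one non-significant stratum as evidence that the effects differ.

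**Working it through.** **1. The plan's own figure.** The plan gives no number for the subgroup analysis. Its sample size rests on the within-between (group by time) interaction: "effect size = 0.25, *α* = 0.05, 1 − β = 0.95, and the number of groups = 3". With three visits as stated, and correlation 0.5 and full sphericity assumed, λ = f²·N·m/(1−ρ):

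- N = 54: λ = 0.0625·54·3/0.5 = 20.25, df 4 and 102, power 0.958.
- N = 51: λ = 19.125, df 4 and 96, power 0.946.

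So 54 is the smallest multiple of three that reaches 0.95, and 54/0.9 = 60. The stated size reproduces, but it is for group by time and does not cover the subgroup question.

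**2. Assumptions.** None of these is in the protocol: FMA-UE SD 8; within-person correlation ρ of 0.5 to 0.7; 10 early and 10 late patients per arm; no true difference in the RTFE effect between strata; early patients gain δ points more in every arm, at both follow-up visits. I show δ = 2, 4, 6 and 8, that is 0.25 to 1.0 SD.

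**3. Reading A: time by stratum.** This is the comparison that the text describes. The early-minus-late profile is (0, δ, δ). Centred, it is (−2δ/3, δ/3, δ/3), with sum of squares 2δ²/3. With n patients per stratum,

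λ = (n/2)·(2δ²/3) / [SD²·(1−ρ)], df 2 and 2(2n−2).

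Example for the RTFE arm only: n = 10, δ = 6, ρ = 0.5 gives λ = 5·24/(64·0.5) = 3.75, df 2 and 36, rejection 36%. For all 60 patients (n = 30), λ = 15·24/32 = 11.25, df 2 and 116, rejection 85%.

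| Extra early gain | RTFE arm only, ρ 0.5 / 0.7 | All 60, ρ 0.5 / 0.7 |
|---|---|---|
| 2 points | 8% / 10% | 15% / 23% |
| 4 points | 18% / 28% | 49% / 72% |
| 6 points | 36% / 57% | 85% / 98% |
| 8 points | 59% / 82% | 98% / 100% |

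Each entry is the chance of a significant result when RTFE works equally well in both strata. Simulation (10,000 trials per setting, ρ = 0.5) agrees: 0.08, 0.18, 0.36 and 0.59 in the RTFE arm; 0.16, 0.49, 0.85 and 0.98 in all 60 with no RTFE effect. A 13:7 early-to-late split gives the same pattern.

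**4. Reading B: time by arm, separately in each stratum.** Recovery common to all arms cancels, so this reading is not biased by it. But no test compares the strata. If each stratum's test rejects with probability p, exactly one is significant with probability 2p(1−p).

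- No RTFE effect: p ≈ 0.05, 2·0.05·0.95 ≈ 10%.
- Equal effect of 0.5 SD: p ≈ 0.175, about 29%.
- Equal effect of 1.0 SD: p ≈ 0.615, about 47%.

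Simulation gives 9–10%, 28–30% and 47–48%.

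**5. The term that answers the question.** In the same simulations, time × group × stratum rejects in 4.7–5.3% of trials for every extra early gain from 0 to 1 SD. Its power is low: about 0.11, 0.35 and 0.69 when the true extra RTFE benefit in early patients is 0.5, 1.0 and 1.5 SD.

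**6. Precision.** For arm by stratum on week-6 FMA-UE adjusted for baseline, the RTFE–RT interaction involves four cells of 10. SE ≈ 8·√(1−ρ²)·√(4/10), which is 4.4 points at ρ = 0.5 and 3.6 at ρ = 0.7. With 60 − 7 = 53 df, the 95% CI half-width is about 8.8 and 7.2 points.

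**The case against.** **The analysis is exploratory.** True, and the section says so. It does not touch the week-6 primary comparison, the sample size or the three-group null hypothesis. The subgroup is the randomization stratum with a fixed cut, not a post hoc choice. A reader might infer that the trial's main conclusion is compromised; the documents do not support that. This limits the grade but does not make the named method suitable.

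**Two-factor could mean arm and stratum, with time on top.** The subgroup factors are not listed, and that model would contain the right interaction. But the same section uses the term for time and group, so this is the less natural reading. If it was intended, one phrase settles the matter.

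**Spontaneous recovery need not be reported as an RTFE effect.** A reader might infer that the plan leads to this error. It is a risk only under time by stratum; within-stratum analyses are free of it. Nothing in the article says how a significant result would be interpreted, so the supported wording is that it could be misread.

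**The size depends on unsupported inputs.** This stands. Taking only a 6–8 point recovery gap would suggest 36–82% (RTFE arm) or 85–100% (all 60). The protocol gives no basis for that gap, and 2–4 points gives 8–28% or 15–72%. The all-60 figures also pool the arms, which fits a question about RTFE least well.

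**A statistical analysis plan may settle it.** It may, but the protocol has already named a method, and that method does not fit the question.

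**Conclusion.** The point holds as a moderate, wrong-as-written fault. The article asks an effect-modification question and assigns a method that, on either natural reading, lacks the term needed to answer it. That conclusion is structural and needs no assumed values.

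The size does need them. Under the assumptions in the working, the time-by-stratum test signals falsely in about 8–82% of trials in the RTFE arm, or 15–100% in all 60, against about 5% for the correct term. Separate stratum tests disagree in about 10% of trials with no effect and up to about 48% with an equal 1 SD effect. These are wide ranges because the SD, correlation, split and recovery gap are all unknown. The Discussion's remark on neuroplasticity supports expecting some gap, but not any particular size.

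It is not a must-fix: the analysis is secondary, already called exploratory, and separate from the primary test.

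**What to change.** In Statistical methods, name the term. The smallest change keeps the protocol's own model and states that the subgroup question is tested by the time × group × stratum interaction. The alternative is one model for week-6 FMA-UE with arm, stratum (<3 versus ≥3 months), arm by stratum and baseline FMA-UE, which asks the same question at the primary time point. Either way, specify RTFE versus RT as the contrast of interest. Report the RTFE–RT difference in each stratum and the interaction estimate, all with 95% CIs, and do not infer a difference from one stratum being significant and the other not. Keep the exploratory description.

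The cost is wording only: no extra patients, visits or data. The downside is that with about 10 patients per cell the interaction interval will be wide and the result will often be inconclusive. The report should say so.

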## Methods

### Study design

This single-blind (assessor blinding), three-arm, superiority RCT will include 3 evaluation sessions (baseline, the end of interventions (6 weeks) and the end of follow-up (3 months)), and 6-week interventions for three groups (CRTs, RT and RTFE). The flow chart of this study is shown in Fig. 1. The SPIRIT figure is shown in Fig. 2.

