#### Discontinuing criteria

Withdrawing will be in consideration if:Participants decide to withdrawParticipants develop serious diseases such as serious heart attacks and strokeTherapists, stroke physicians and investigators may also withdraw participants if they think this trial is no longer in patients’ interest; for example, continuing this trial might induce more adverse events

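### Five imputations are paired with repeated-measures F and rank tests that Rubin's scalar rules do not pool; a mixed model for week-6 FMA-UE would avoid the problem at little cost

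*Protocol article*

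**What the plan says.** All of the relevant text is in the Statistical methods section of the protocol article.

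- Missing data: "Multiple imputations based on 5 replications and the Markov-chain Monte Carlo method in the SAS MI procedure will be used to handle the missing data".
- Main analysis: "Two-factor repeated-measures analysis of variance (ANOVA) will be used for the statistical analysis for all outcomes with the sphericity test before analysis".
- First switch: "If the data is dissatisfied with the sphericity test, the Green-house-Geisser method will be used to correct it".
- Second switch: "Scheirer-Ray-Hare test will be used if the data are not satisfied with normal distribution".
- Software: "All data will be analysed by Statistical Package for the Social Science (SPSS) version 26.0 software".
- Principle: "All analyses in this trial will follow the intention-to-treat principle".

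The Study design section sets three assessments (baseline, 6 weeks, 3 months) in three arms. The Primary outcome section places the primary endpoint, FMA-UE, at the end of week 6. The Sample size section plans for 10% attrition, and the Discussion counts the imputation strategy among the trial's strengths.

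**The concern.** Multiple imputation yields five completed datasets and so five analyses, which must be turned into one result. The standard method, Rubin's rules for a scalar, needs an estimate and a standard error from each dataset. The analyses named here are omnibus tests, and they fit that method badly in three ways:

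- **Form of the statistic.** The group-by-time interaction is tested by a multi-df F, or by a rank H in the fallback. Neither is an estimate with a standard error.
- **Switching.** The sphericity and normality checks depend on the data. Run on five completed datasets, they can disagree. Some datasets could then give an uncorrected F, some a corrected F with its own epsilon, and some an H.
- **Conflicting models.** MCMC imputation draws from a multivariate normal model, while the rank test is reserved for data judged not normal. In that branch the imputed values come from a model the analysis has just rejected.

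What is at stake is the type I error of the main test. An analyst without a suitable combining rule might average the statistics or analyse one completed dataset. Both treat imputed values as if they had been observed.

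**Working it through.** **1. The plan's own figure.** Inputs from the Sample size section: f = 0.25, alpha = 0.05, power 0.95, 3 groups, within-between interaction. Three time points come from Study design. Correlation 0.5 and epsilon 1 are not stated and are assumed.

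- Noncentrality = f² × N × m / (1 − rho) = 0.0625 × 54 × 3 / 0.5 = 20.25
- df1 = (3 − 1)(3 − 1) = 4; df2 = (54 − 3)(3 − 1) = 102
- Power = 0.958, and 54 is the smallest multiple of 3 that reaches 0.95. Attrition: 54 / 0.9 = 60.

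The stated 54 and 60 are reproduced. The test that was powered is the 4-df interaction.

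**2. What Rubin's scalar rules need.** With m = 5 estimates Q_i and variances W_i, the pooled estimate is the mean of the Q_i. Its total variance is T = mean(W_i) + (1 + 1/5)B = mean(W_i) + 1.2B, where B is the variance of the Q_i between imputations. A 4-df F or a rank H supplies neither Q_i nor W_i.

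**3. Is five too few?** Relative efficiency is 1 / (1 + gamma/m). At 10% missing information it is 1 / (1 + 0.10/5) = 0.98; at 20% it is 1 / (1 + 0.20/5) = 0.96. The number of imputations is not the problem.

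**4. Does the combining step matter?** A simulation under the null used 20 patients per arm, 3 times, equal correlation 0.5 and five Bayesian normal imputations with arm in the model. Dropout was completely random and monotone: half of it occurred before week 6 and half between week 6 and 3 months. Each setting had 2,000 trials. The interaction F was tested on 4 and (60 − 3) × 2 = 114 df. The D2 rule combines the five statistics d_i = 4F_i through r = 1.2 × var(√d_i), as D2 = [mean(d)/4 − 1.5r] / (1 + r).

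Type I error at nominal 0.05:

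| Overall dropout | Mean of five F | One completed dataset | D2 rule | Complete cases |
|---|---|---|---|---|
| 10% (planned) | 0.080 | 0.081 | 0.052 | 0.049 |
| 20% (assumed) | 0.122 | 0.131 | 0.043 | 0.047 |
| 30% (assumed) | 0.173 | 0.188 | 0.047 | 0.054 |

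Simulation error is about ±0.01 (1.96 × √(0.05 × 0.95 / 2,000) = 0.0096). At 10% dropout, 0.10 × 60 = 6 patients on average lack the 3-month value, and about 3 of them also lack week 6. The equal correlation means that sphericity holds, so the Greenhouse-Geisser and Scheirer-Ray-Hare branches were not simulated.

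**The case against.** The strongest reply is that the problem can be solved within the plan. Multi-df statistics can be combined after imputation: D1 and D3 work from estimates or likelihoods, and D2 from the test statistics. D2 held its level in the simulation. A combining rule is the kind of detail an article may leave to an analysis plan that is not shown, and nothing in the article prescribes averaging F values. Comparisons at a single time within the simple effects tests can also be written as mean differences, which the scalar rules do pool. All of this stands. It rules out saying that the five analyses have no combined answer, and the lack of a stated rule is not in itself the fault. What remains is that the article fixes an awkward pairing, with two data-dependent switches and a conflict between the normal model and the rank test, when a simpler analysis would address the stated endpoint directly.

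A reader might infer several stronger points that the document does not support:

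- **Withdrawn patients are imputed as if still treated.** The Discontinuing criteria say that "investigators may also withdraw participants if they think this trial is no longer in patients" interest, but not that assessment then stops. No imputation model or missingness assumption is stated.
- **The plan is not intention to treat.** It analyses patients as randomised and imputes missing values. Imputation under missing at random does not contradict that. A mixed model makes the same assumption.
- **The RTFE-RT difference is overstated by 10% to 20%.** That needs unassessed withdrawals, imputation within arm that ignores treatment status, fully RT-like outcomes in those patients and, for 20%, an invented 4 of 20 RTFE withdrawals.
- **A missed 3-month visit deletes a valid week-6 value.** This would happen in a complete-case ANOVA, but the planned imputation avoids it.
- **SAS and SPSS cannot be used together.** Imputing in one and analysing in the other is feasible. The fault is only that the text assigns all analysis to SPSS.

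**Conclusion.** The point holds as a cheap improvement. The article joins five normal-model imputations to omnibus F and rank tests that the usual pooling rules do not handle, and it ties no suitable rule to them. If the F values were averaged, or one completed dataset used, the interaction test would run at about 0.08 instead of 0.05 at the planned 10% attrition. With a valid multi-df rule it would run at about 0.05. These figures assume correlation 0.5, sphericity, completely random dropout and normal data. They show what an unsuitable shortcut would cost; they do not describe something the plan says it will do. No direction of bias and no departure from intention to treat has been shown.

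**What to change.** 1. Make the primary analysis a likelihood-based mixed model for FMA-UE at week 6 and 3 months. Include arm, visit and arm by visit, and adjust for baseline FMA-UE and the randomisation stratum (under 3 months, or 3 months and over, since stroke). It uses every observed value without imputation.
2. Report the week-6 RTFE-RT difference with its confidence interval. This is a single contrast at the stated primary time point.
3. Keep multiple imputation as a sensitivity analysis that pools this contrast by Rubin's rules. If the interaction F is kept, name a multi-df rule such as D2 in advance.
4. Because the mixed model also assumes missing at random, consider a reference-based imputation as a further sensitivity analysis.
5. Reconcile the software statements, saying which program imputes and which one analyses.

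The cost is a few sentences in the protocol and analysis plan and a little more analysis work. The visits, baseline score and stratum are already planned, so no new data are needed.

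### Five imputations leave avoidable seed noise in the p < 0.05 verdict (about 2% to 8% of trials at the planned 10% attrition); at least 50 would cut it by about two thirds for seconds of computing

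*Protocol article*

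**What the plan says.** Under Statistical methods, missing data are to be handled by "Multiple imputations based on 5 replications", drawn by MCMC with the MI procedure of SAS. The same section sets significance at a P "value less than 0.05" and applies a two-factor repeated-measures ANOVA to every outcome. No reason is given for five imputations.

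The only missing-data rate in the protocol is under Sample size: "Considering 10% attrition, we inflated the total sample size to 60". That section plans for high power on a conventional effect: "the effect size of 0.25 was applied", with "1 − β = 0.95, and the number of groups = 3", for the "within-between interaction" of a repeated-measures ANOVA.

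**The concern.** Each imputed dataset contains random draws, so a pooled test statistic from a finite number of imputations, m, depends partly on the seed. The noise shrinks as m grows. When a result lies close to the threshold, a small m can let the seed decide whether p falls below 0.05. The protocol reads its outcomes against that threshold, so it is worth asking how often this would happen at m = 5 and how much a larger m would help.

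The number of imputations involves no real trade-off in a trial of 60 patients and three visits. More imputations change neither the imputation model nor the estimand nor the analysis, and the run still takes seconds. That last statement is general computing experience, not something the protocol says.

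**Working it through.** **Inputs from the protocol.** m = 5 and the 0.05 threshold (Statistical methods); 10% attrition, f = 0.25, power 0.95, three groups, 60 patients at 20 per arm (Sample size); three assessments (Study design).

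**Assumptions not in the protocol.** Within-patient correlation 0.5 (0.7 as a sensitivity value), sphericity, normal data, values missing at random, and patients who drop out missing both post-baseline visits.

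**1. The plan's own sample size.** The non-centrality for the within-between interaction is λ = f² × N × 3 / (1 − ρ).
- N = 54: λ = 0.0625 × 54 × 3 / 0.5 = 20.25, with df 4 and (54 − 3) × 2 = 102. Power is 0.958.
- N = 51: power is 0.946, below target.
- Attrition: 54 / 0.9 = 60.

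The stated 54 and 60 are reproduced, so 95% power at f = 0.25 with 10% attrition is the right reference case.

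**2. Efficiency of the estimate.** In the simulations below, 10% missing gave a fraction of missing information (FMI) of about 0.09 to 0.10. Relative efficiency at m = 5 is 1 / (1 + FMI/m) = 1 / (1 + 0.10/5) = 0.98.

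**3. Noise in the test statistic.** The between-seed SD of z is about √(FMI/m).
- m = 5: √(0.10/5) = 0.141
- m = 50: √(0.10/50) = 0.045

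One SD either side of z = 2.0 at m = 5 is 1.86 to 2.14, that is p from 0.063 down to 0.032.

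**4. How often two seeds disagree (analytic).** For small noise, the rate is about the density of z at the critical value times the mean absolute difference between two runs, which is (2/√π) × √(FMI/m). This difference is 1.128 × 0.141 = 0.160 at m = 5 and 1.128 × 0.045 = 0.050 at m = 50. The densities are 0.399 at 50% power, 0.280 at 80%, 0.103 at 95%, and 2 × 0.058 = 0.117 under the null (two-sided).

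| Power | m = 5 | m = 50 |
|---|---|---|
| 50% | 0.399 × 0.160 ≈ 6.4% | ≈ 2.0% |
| 80% | 0.280 × 0.160 ≈ 4.5% | ≈ 1.4% |
| 95% | 0.103 × 0.160 ≈ 1.7% | ≈ 0.5% |
| Null | 0.117 × 0.160 ≈ 1.9% | ≈ 0.6% |

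**5. Simulation at 10% missing, m = 5.** Each simulated trial was imputed twice with independent draws. The interaction test used a multivariate pooled F test (2,500 trials per setting). The RTFE versus RT comparison used change to week 6 with small-sample degrees of freedom (6,000 trials per setting, correlation 0.5 and 0.7).

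| Setting | Group-by-time interaction | RTFE vs RT |
|---|---|---|
| Null | 2.7% | 1.5–2.1% |
| Power near 50% | 7.8% (f = 0.15, power 54%) | 6.6–7.1% |
| Power near 80% | 5.2% (f = 0.20, power 83%) | 5.1–5.8% |
| Power near 95% | 1.9% (f = 0.25, power 97%) | 2.0–2.8% |

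**6. Sensitivity to the contrast.** A baseline-adjusted RTFE versus RT contrast at week 6, which is not the planned analysis, gave 8.4% and 8.7% in two separate runs at a standardised difference of 0.5 (power about 41%). At a difference of 0.8 it gave 5.9% and 7.2%. These lie at or slightly above the top of the ranges in step 5.

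**7. Effect of more imputations.** For the interaction test at f = 0.15, disagreement falls from 7.8% (m = 5) to 3.7% (m = 20) and 2.3% (m = 50). The formula gives the same proportional fall: 1 − √(5/50) = 68%.

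**The case against.** The strongest reply is that five imputations are adequate here. Rubin's rules carry the extra (1 + 1/m) term and adjusted degrees of freedom, so finite-m noise is already in the standard error. There is no bias and no inflated type I error, and efficiency is 98%. At the planned 95% power, going from 5 to 50 imputations changes the analytic disagreement rate from 1.7% to 0.5%, about 1.2 percentage points. All of this stands. It makes the point a modest improvement, not a correction.

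Three stronger readings are tempting, and the documents do not support them.
- **That about 1 in 12 analyses would flip with a new seed.** That rate (8.3%) is a near-worst case. At 10% missing it is approached only when power is near 50%. Otherwise it needs about 20% missing with power near 80%, or about 30% missing with power near 90% to 95%. The protocol plans for 10% attrition and 95% power.
- **That results near the threshold are likely in a trial of this size.** By normal approximation, the chance of p between 0.03 and 0.06 is about 3% under the null or at 95% power, 9% at 80% power and 11% at 50% power.
- **That the primary result would not be reproducible.** A recorded seed reproduces any run exactly, whatever m is. Recording it is a programming or analysis-plan detail, and its absence from a condensed article is no finding.

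In favour of acting, the 95% power rests on a conventional effect size, adopted because the authors found no suitable study. Lower true power is therefore possible, and the higher rates with it.

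**Conclusion.** The point holds as a small, free improvement. Five imputations are valid, but they leave more seed dependence in the p < 0.05 verdict than necessary. At 10% missing, disagreement between seeds is about 2% at the planned power or under the null, about 4% to 6% at 80% power, and about 6% to 8% near 50% power. With 50 imputations the range is roughly 0.5% to 3%.

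The sizes rest on the assumptions listed in the working. Monte Carlo error in the simulated rates is about 0.2 to 0.7 percentage points. More missing data than planned would raise the rates: at 20% missing they are 4.1% to 5.0% near 95% power and 11.3% to 12.4% near 50% power.

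**What to change.** In Statistical methods, replace five replications by at least 50 imputations. Leave the imputation method, the analysis model and the rest of the missing-data plan as they are. The cost is one number in the text and seconds of computing; there is no statistical downside.
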